# A multi-centre, parallel-group, randomised controlled trial to assess the efficacy and safety of eurythmy therapy and tai chi in comparison with standard care in chronically ill elderly patients with increased risk of falling (ENTAiER): a trial protocol

**DOI:** 10.1186/s12877-020-1503-6

**Published:** 2020-03-17

**Keywords:** Aged, Falls, Prevention, Exercise, Tai chi, Eurythmy therapy, Chronic disease

## Abstract

**Background:**

In elderly poeple, multimorbidity and polypharmacy increase while sensory, motor and cognitive functions decrease. Falls occur in 30% of people aged 65 years and older at least once per year, with injuries at 10–20%. Reducing falls and enhancing physical, emotional and cognitive capacities are essential for healthy aging despite chronic disease. Eurythmy therapy (EYT) and Tai Chi train balance, mobility and concentrative and sensory capacities.

**Methods:**

In eight trial sites (academic or community hospitals), 550 outpatients aged 65 years and older with chronic disease and increased risk of falling (history of imbalance, Berg Balance Scale (BBS) score ≤ 49) will be randomly assigned (1:1:1) to receive either EYT or Tai Chi (each provided in one-hour group sessions, twice, later once per week plus practice at home, for over 24 weeks) added to standard care or standard care alone. Standard care includes a detailed written recommendation on fall prevention and the visit of a primary care doctor. Seniors living a reclusive life or economically disadvantaged elderly will be particularly addressed. A motivation and communication concept supports the trial participants’ compliance with trial procedures and practicing. Public and patient representatives are involved in the planning and conduction of the trial. Falls will be documented daily in a diary by the participants. These falls as well as injuries and complications will be ascertained during monthly phone visits. The falls efficacy scale, BBS, cognition (MoCA), Mood (GDS-15), quality of life (SF12), instrumental activities of daily living (IADL), use of medical and non-medical services (FIMA) and adherence will be assessed at months 3, 6, and 12 and inner correspondence with practices (ICPH) at month 6. The trial is funded by the Federal Ministry of Education and Research (BMBF 01GL1805).

**Discussion:**

This study will determine whether EYT and Tai Chi reduce falls, injurious falls, fear of falling and healthcare utilisation and improve mobility, cognition, mood, quality of life and functional independence. A reduction of fall risk and fear of falling and an improvement of mobility, autonomy, quality of life, mood, and cognition are highly relevant for older people to cope with aging and diseases and to reduce healthcare costs.

**Trail registration:**

www.drks.de. DRKS00016609. Registered 30th July 2019.

## Background

Eighty percent of older adults have at least one chronic disease and 65% have at least two [1, 2], leading to an increased risk of polypharmacy [3]. Sensory functions, movement and cognitive capacity impair with aging, thus increasing immobility, frailty, dependence, health-care utilisation, risk of falling and fear of falling [3–6]. The incidence rate of falls of people aged 65–90 is 0.3–0.4 and that of ‘recurrent falls’ is 0.1 per person and year [7], and 21–85% of older adults are afraid of falling [8]. About 10–20% of falls lead to injuries, 5% to fractures and 1–2% to femoral neck fractures [5]. After femoral neck fractures, only 33–40% of patients regain their previous basic everyday competences (e.g., eating and body care), only 14–21% resume their competence for instrumental activities (e.g. shopping and phone calls) and 30% die within 1 year [5, 9]. After falls and hip fracture, 30–50% of people express their fear of falling, which reduces physical activity, mobility and self-confidence. The rates of falls, social isolation, institutionalisation and mortality have increased [5, 9]. The risk factors for falls in the elderly include the following: history of a fall, lower-extremity weakness, impairment of cognitive and sensory functions (e.g. proprioceptive sensitivity, vestibular system, vision and hearing), chronic disease (e.g. cerebrovascular or cardiovascular, Parkinson’s disease, osteoarthritis of the knee and diabetes), drugs particularly those affecting the central nervous system, type of footwear and safety hazards in the home environment [10, 11].

To interrupt the vicious circle of a physically inactive lifestyle, social isolation, reduced autonomy, increased risk of falling, morbidity [3–5, 12–14] and to enable healthy aging despite chronic disease, reducing risk and fear of falling and enhancing the physical, mental and cognitive capacities are essential [3–5]. Recommended for fall reduction and improved mobility are strength and balance training, treating osteoporosis, optimisation of medications, vision, safe homewear and environmental factors [15–17]. However, older people often do not perform the recommended exercise training, and only 14% of people aged 70–79 are physically active as recommended (at least 2.5 h per week) [18]. The reasons for avoiding exercise are health issues, negative experience and experiencing exercise like it’s a ‘chore’ and a ‘big deal’. Structured ‘artificial’ activities, such as using an exercise bicycle, usually have negative connotations. Support for regular exercise is an appreciable and encouraging social-context indoor activity that is achievable in comparison with ‘hard work’, and it begins with minimal-intensity exercises that are interesting, safe and pleasurable and that cause noticeable improvements in mood, confidence, energy and self-perceived risk of falls and injuries [19–21].

Regular Tai Chi, a mind–body intervention, can reduce falls by 19% [rate ratio (RaR): 0.81, 95% CI: 0.67–0.99], risk of falling by 20% [risk ratio (RR): 0.80, 95% CI: 0.70–0.91] and fear of falling. Altogether, exercise reduces falls by 23% (RaR: 0.77, 95% CI: 0.71–0.83) and risk of falls by 15% (RR: 0.85, 95% CI: 0.81–0.89). Although less certain, it may also reduce the number of people experiencing fall-related fractures (RR: 0.73, 95% CI: 0.56–0.95) and falls requiring medical attention (RR: 0.61, 95% CI: 0.47–0.79) [22–26]. Particularly important are exercise programmes that involve balance and functional exercises [26]. Repeating (i.e. weekly or biweekly) exercises under instruction and close observation are important for learning, training and individually tailoring the exercises to the capabilities of the elderly. Tai Chi intervention should involve at least 50 h of practice to be effective [27].

Integrative and mind-body-based interventions have gained increasing importance and popularity. Particularly, people entering the age of 60+ can be expected to have a strong preference for integrative mind-body interventions compared with the artificial training of strength and balance [35–37]. As actual training depends on motivation and availability, an assessment of these interventions in health outcomes and inner involvement in chronically ill elderly people with increased risk of falling is of major importance. The underlying question is whether mindfulness exercise can interrupt the vicious circle of chronic disease, falls, inactivity, loss of independence and reduced quality of life.

### Objectives

The primary objective is to determine whether EYT and Tai Chi can reduce the risk of falling (i.e. experiencing at least one fall), which usually marks the beginning of dependency and the decline of mobility. This is assessed by comparing EYT plus standard care, Tai Chi plus standard care and standard care alone with respect to the risk of falling over a time period of 6 months. The secondary objective is to determine whether EYT and Tai Chi can improve mobility and balance and reduce injuries through falls and fear of falling, which are usually the primary threat to mobility. The follow-up question is to determine whether this leads to the better management of daily tasks and a better health-related quality of life, cognition and mood and whether it affects healthcare utilisation and costs. Finally, the inner correspondence of the participants with the practices and how well they adhere to them will be assessed.

### Study design

Multi-centre, randomised controlled, open-label, confirmative trial with two active and one control parallel groups.

## Methods: participants, interventions and outcomes

### Study setting and time schedule

Eight qualified trial sites are used in this trial: Medical Center – University of Freiburg (Centre for Complementary Medicine), Tübingen, (Institute of General Practice and Interprofessional Care), Witten Herdecke (Institute of Integrative Medicine), Duisburg-Essen (Department of Naturopathy and Integrative Medicine), Ulm (Integrative Medicine), Charité, Berlin (Immanuel Hospital), Havelhöhe Hospital, Berlin and Filderklinik, Filderstadt. The University Centre for Complementary Medicine and the Clinical Trial Unit (CTU) of the Medical Centre–University of Freiburg organise and manage the trial. Patient recruitment is planned from the third quartile of 2019 to the second quartile of 2021. The follow-up will end in the second quartile of 2022.

### Key eligibility criteria

Included will be adults who are at least 65 years, have a chronic disease (e.g. musculoskeletal, neurological or cardiovascular), have an increased risk of falling [Berg Balance Scale (BBS) score 49 or less and a self-reported history of imbalance], are able to participate in 1 h group-based sessions and are able to leave home on their own. There is no restriction with respect to their domicile.

Excluded will be patients with medical conditions limiting participation (e.g., terminal illness, heart failure NYHA III-IV, unstable angina pectoris, uncontrolled seizure disorder, decompensated lung disease, cancer in the advanced stage, chemo- or radiotherapy ongoing or during the last 3 months or amputation of one or both legs); complete dependence on a rollator (wheeled walker); major visual, hearing or language problems affecting the understanding of trial documents and procedures; major cognitive impairment (MoCA score 18 or less); conditions affecting the participation of group classes (e.g. high risk for individual support, urge incontinence, personality disorder and substance use disorders); life expectancy less than 1 year; permanent confinement to bed to be expected in less than a year; participation in regular Tai Chi or EYT exercises within the last 6 months and participation in vigorous sports for exercise within the last month.

A specific recruiting strategy will strengthen the enrolment of elderly people who are economically disadvantaged and living a reclusive life.

### Interventions

Participants will be randomly allocated to receive standard care plus EYT or plus Tai Chi or standard care only (control).^1^

#### What

EYT [30, 31] and Tai Chi [22–25] exercises are described in a manual. They are derived from previous studies investigating fall prevention or based on recommendations by experts. They have been reviewed by Tai Chi teachers, EYT therapists and external experts.

‘Standard Care’: participants receive a well-described brochure that recommends evidence-based measures to reduce risk of falling (e.g. training balance, strength, flexibility, endurance; medication modification; safe home environment; bone health; safe footwear; assistive devices) and provides addresses for more information or support [38]. Participants will also be recommended to visit their primary care physician to receive care based on evidence-based guidelines to prevent falls [39] or to manage multi-morbidity [40] or polypharmacy [41].

#### Who provides

EYT is instructed and guided by a certified EYT therapist (5 1/2 years of training according a standardised curriculum). Tai Chi is instructed and guided by a teacher with at least 500 h of training according to a standardised curriculum or an equivalent of 500 h of own teaching. Therapists and teachers are experienced in instructing and guiding the exercises. They are invited to practice together before the commencement of the trial. Standard care is provided and organised by the participants’ primary care doctor or consultant according to the patients’ own discretion. The brochure [38], which also enables participants to conduct self-help, is handed over by the trial sites.

#### How

EYT and Tai Chi will be provided in one-hour sessions, in groups of 4–6 participants, and may include a resting time (approximately 15 min) in the end. For practicing at home, participants receive oral, written (manual) and audio-visual instructions.

#### Where

Group classes will be held in appropriate rooms of sufficient size, which provide one stable and safe chair per participant and are accessible for those with disabilities, within reach of public transportation and, if possible, located nearby the participants. For home training, participants receive safety instructions.

#### When

Group sessions will take place twice a week during weeks 1–12 and once per week during weeks 13–24. The intensity is higher in the first weeks, taking into account the learning curve, and is reduced later when individual practicing has become routine. The participants are instructed to practice exercises at home for a minimum of 20 min during three non-class days.

#### Tailoring

Tai Chi and EYT follow the manuals but can be individually tailored to the capabilities of the participants.

#### How well

The participants will keep training diaries. The therapists and teachers will keep attendance lists and lists of deviations from the planned exercises.

#### Additional interventions

All other treatments are allowed outside the trial except EYT or Tai Chi/Qigong/Yoga in the non-EYT or non-Tai Chi groups, respectively.

### Outcomes

*Primary outcome* Risk of falling is the incidence of experiencing at least one fall within 6 months. A fall is defined as ‘an unexpected event in which the participants come to rest on the ground, floor or lower level’ [42]. The frequency of falls is self-reported daily in the fall diaries and ascertained during the monthly phone calls. Its assessments follow international guidelines [42].

*Secondary outcomes* are the risk of falling at month 12; the number of falls and injurious falls categorised into ‘moderate’ (sprains, bruises, scrapes, joint injuries and needing medical care) and ‘serious’ (fracture, head injury, tendon rupture, inpatient care and requiring stitches) [43]; balance and mobility (BBS [44]); cognition (MoCA [45]); fear of falling (short FES-I [46]); mood (GDS-15 [47]); health status (SF-12 [48]); instrumental activities of daily living (IADL [49]); use of medical and non-medical services (FIMA [50]); medications (total number and classes of fall-risk-increasing drugs [51]); adherence to practicing in groups and at home (participants’ lists and training diary); inner correspondence/peaceful harmony with practices (ICPH [52]), use of standard fall prevention measures and subjective estimation of motivational support; and contamination with Tai Chi or EYT in the non-Tai Chi and non-EYT groups (self-designed questionnaires, see Supplementary file 1, 2, 3 and 4)).

### Complications

The complications that can arise from EYT, Tai Chi or other exercises will be collected monthly. A complication is any untoward medical occurrence such as any unfavourable and unintended sign, symptom, or disease that is possibly related to the study intervention. Not regarded as complications are conditions that were already present at the time of the informed consent or aching muscle, which is to be expected. Starting with the open questions, participants are asked about any untoward medical occurrences or unplanned medical visits. In case of a possible relation to the intervention, these occurrences are documented, including severity and outcome. Moreover, therapists or teachers can inform the trial sites about the complications. Falls and injurious falls are documented as primary outcomes, and injuries are reported as complications in case they occurred during training. Further information on safety will be derived from the FIMA, which assesses healthcare utilisation such as physician contacts and hospitalisations.

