### Blinding and minimising risk of bias

The blinding of the Tai Chi and EYT group and the standard care group to their allocation is not possible because it is obvious in which group the participants are randomised, as all three trial interventions differ substantially. The outcomes are either directly reported by the participants (falls, questionnaires) or in close communication with the participants (falls, complications, BBS, MoCA, IADL). Therefore, also a reliable blinding of the outcome assessment to participant allocation is not possible. Outcome assessors are instructed by a written guide to start with open and general questions and to avoid mentioning the group allocation as long as possible. Since the electronic case report forms differ depending on randomized treatment, the statistical analysis will not be blinded, but all confirmatory analyses are prespecified in the clinical trial protocol and decisions on analysis data sets will be finalized without access to the unblinded data. Concealment of the randomisation will be guaranteed to minimise selection bias. All assessments will be conducted in a comparable setting and time. The primary outcome parameter is clearly defined and described in detail [42]. The combination of prospective, daily, participant-completed falls diary and monthly calls is regarded to be reliable and captures most of the falls among seniors [55]. To reduce incomplete outcome data, travel costs for public transportation are refunded, and the trial sites may conduct the follow-up visits at the participants’ home. Two of the groups receive interventions in a comparable setting, support and frequency. The third (control) group, although not offered regular training sessions, can still avail of such opportunities through the addresses in the brochure, the general courses in their city or their primary care physician. They receive human attention through an appreciating communication with the trained study personnel and their primary care doctors, other consultants and medical referrals at their discretion and informed by evidence. The patient informed consent (form) makes no remarks on the potential efficacy of EYT or Tai Chi to reduce expectancy bias. Publication bias will be reduced by study registration in the trial registers, the publication of the trial protocol and the results and the support of open data.

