## Methods: data collection, management and analysis

### Data collection methods

BBS, MoCA, IADL and the complications are assessed by the study personnel.

The FES-I, GDS-15, SF-12, ICPH and FIMA questionnaires, the falls and training diaries and the self-designed questionnaires (see Supplementary file 1, 2, 3 and 4) are filled in by the participants in the same environment, which is quiet and respectful of the subject’s privacy. As much as possible, the outcome measures are assessed at a consistent time of the day and consistent with the medication cycles, particularly in participants with conditions like Parkinson’s and multiple sclerosis. The data obtained by the investigators are kept in source documents and directly entered in a trial-specific electronic case report form (eCRF). The patient-reported questionnaires are stored as the participants’ source documents, and a duplicate is sent to the CTU in Freiburg to be entered in the eCRF.

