For the analysis of the secondary endpoint total number of falls per participant within 6 months after handing out the study book, a negative binomial regression model will be used to test the efficacy of EYT versus Tai Chi versus standard care. A negative binomial is preferred over a Poisson regression because of the potential overdispersion. Fall rates for participants with follow-up times of less than 6 months will be adjusted by accounting for their exposure time. The model will include intervention type, trial site, BBS score and age as the independent variables. The incidence rate ratios between interventions will be calculated from the model with a two-sided 95% CI. To consider the potentially present excess of zeroes, a zero-inflated negative binomial model will be used as a sensitivity analysis. Other secondary endpoints will be analysed with the appropriate regression models.

Safety analyses will be performed for all participants for whom one of the interventions is started, and participants will be analysed according to the intervention received. The rates of adverse events and serious adverse events will be calculated with a two-sided 95% CI. No formal interim analyses of the efficacy endpoints will be performed.

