No blinding is possible for exercise classes, and no intervention mimicking EYT or Tai Chi while lacking any specific effects for fall prevention can be found. Potential competing interventions, such as stretching, life reviewing groups and training in health competencies and literacy, if well designed and conducted, all have specific effects on the risk factors related to falls. However, if they are clearly designed to lack all specific effects on any risk factors, then they are ethically questionable, and the PPR voted against them. A waiting list control has been discussed to have nocebo effects, leading to an overestimation of the effects [66]. Therefore, a three-arm design, which compares a highly investigated versus a scarcely investigated intervention versus a standard care only group, is chosen.

We may document more complications in the EYT and Tai Chi groups in comparison with the control group in case the participants in the intervention groups practice more often and more intensely. Therefore, more untoward medical events may be potentially linked to the exercises. We reduce this bias by presenting open questions and avoiding any influence through suggestive questions. Furthermore, we would be more concerned by an underreporting of potential complications, which is not to be expected. The net risk necessitating the medical and non-medical services (FIMA) will be regularly assessed without risk of bias.

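### Safety data are filtered by an unblinded relatedness judgement when they are recorded, so the promised adverse event and serious adverse event rates would be rates of possibly related complications only

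*Protocol article*

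**What the plan says.** The Complications section of the protocol article builds relatedness into its definition. A complication is an untoward occurrence such as an "unfavourable and unintended sign, symptom, or disease that is possibly related to the study intervention". The monthly enquiry is wider than that: "participants are asked about any untoward medical occurrences or unplanned medical visits". The record is narrower again: "In case of a possible relation to the intervention, these occurrences are documented, including severity and outcome".

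The Data collection methods section says who does this: "BBS, MoCA, IADL and the complications are assessed by the study personnel". The section on blinding lists complications among the outcomes obtained in close communication with participants, and concludes that "also a reliable blinding of the outcome assessment to participant allocation is not possible".

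The safety paragraph under Statistical analysis uses different terms. "Safety analyses will be performed for all participants for whom one of the interventions is started", grouped by the intervention received, and "The rates of adverse events and serious adverse events will be calculated with a two-sided 95% CI". The article defines neither adverse event nor serious adverse event, and describes no capture of events regardless of cause.

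Two further statements bear on the point. The Complications section names FIMA, the service-use questionnaire, as an additional safety source covering physician contacts and hospitalisations. The Discussion accepts that more events may be attributed to exercise in the two active arms, and then adds: "The net risk necessitating the medical and non-medical services (FIMA) will be regularly assessed without risk of bias".

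**The concern.** The collection rule and the planned analysis do not match. An event that the participant mentions, but that staff do not connect with the intervention, leaves no entry among the complications. A later analysis plan cannot recover it. The safety table would then carry the label of adverse event and serious adverse event rates while holding a causality-filtered subset.

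The filter is also unlikely to act equally in the three arms. Staff know the allocation. Participants in the EYT and Tai Chi arms have trial classes and prescribed home practice to which an event can be linked, and standard care participants do not. A difference in recorded rates could therefore come from attribution alone. A real excess of a harm that nobody recognises as related would be missed in this record. The data monitoring committee is described as reviewing complications, so as described its regular input is the same filtered record.

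**Working it through.** The plan states no safety figure to reproduce. The check is a comparison of text, followed by an illustration with assumed inputs.

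**Capture against analysis**

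| Step | What the article describes | Relatedness filter? |
|---|---|---|
| Monthly open question, all arms | Any untoward occurrence or unplanned visit | No |
| Documentation as a complication | Only if possibly related, judged by study personnel | Yes |
| Planned safety analysis | Rates of adverse events and serious adverse events | None stated |

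**Sources that bypass the filter**

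- *Falls and injurious falls.* Compared in all arms whatever their cause. The serious category covers fracture, head injury and inpatient care, among others. These cover fall-related harm only.
- *FIMA.* Table 1 places it at baseline and at months 3, 6 and 12, in all arms. Participants complete it, and it is described as measuring service use. The article does not say that it records the severity or outcome of an event. It misses harms that led to no contact, and cannot be returned by those who die or withdraw fully.
- *Death.* Described only as a competing event, when no fall has preceded it, in the 6-month primary analysis. Nothing is said about safety reporting of deaths after a fall or in months 7 to 12.

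A serious event unrelated to a fall, such as a cardiac admission, thus has no described record of severity and outcome unless it is judged possibly related.

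**What the filter does to a rate**

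Let r be the true risk of an untoward event and f the share judged possibly related.

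- Recorded risk = r × f. It equals the true risk only if f = 1.
- If r is the same in both arms, the spurious difference = r × (f_exercise − f_control).

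All values of r and f below are assumptions; the article gives none.

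| r | f exercise / control | Recorded risks | Spurious difference |
|---|---|---|---|
| 20% | 30% / 30% | 6% / 6% | 0 points |
| 20% | 30% / 10% | 6% / 2% | 4 points |
| 60% | 30% / 10% | 18% / 6% | 12 points |
| 20% | 10% / 2% | 2% / 0.4% | 1.6 points |
| 60% | 10% / 2% | 6% / 1.2% | 4.8 points |

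The first row shows that equal attribution removes the spurious difference but leaves both rates understated.

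**What an all-cause comparison could deliver**

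With 550 / 3 ≈ 183 participants per arm and an assumed 12-month serious-event risk q of 10%, 20% or 30% in both arms:

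- Expected events per arm = 183 × q = 18.3, 36.6, 54.9.
- 95% half-width of the difference = 1.96 × √(2q(1 − q)/183) = 6.1, 8.2, 9.4 percentage points.

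This is imprecise, but the difference can be interpreted.

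**The case against.** The strongest reply is that this is a deliberate and disclosed choice for a non-drug exercise trial: possibly related complications on one side, all-cause service use and falls on the other. The Discussion admits that attribution may be unequal and relies on open, non-suggestive questions. Assessors are told to avoid mentioning allocation for as long as possible. The article is also a condensation. The full protocol is in a supplementary file not shown, and it may define adverse events and their capture.

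Much of this limits the point, and three stronger readings should be set aside.

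- A reader might infer that harms not recognised as related are never compared between arms, or that deaths and admissions go unrecorded. The documents do not support this. Injurious falls, FIMA hospitalisations and physician contacts, and deaths without a previous fall are all captured without a relatedness judgement.
- A reader might infer that the recorded rate in standard care is zero by construction. The Complications section also covers exercises other than EYT and Tai Chi, the control brochure recommends training, and control participants may join courses. Attribution may be unequal; a structural zero is not what the text says.
- A reader might infer that adverse event rates cannot be calculated at all. That would require knowing that the full protocol contains no wider capture.

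What does not answer the point: open questions improve what is elicited, but the relatedness decision comes afterwards. FIMA does avoid that decision, and in this limited sense the Discussion's remark is fair. It is still self-reported by participants who know their arm, and is lost for those who die or leave fully. Planned follow-up after stopping the intervention and optional home visits reduce this loss but do not remove it.

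**Conclusion.** The point holds in a limited form. The article sets a collection rule that cannot supply the adverse event and serious adverse event rates it promises. Followed as written, it yields rates of possibly related complications, lower than the all-cause rates unless every event is judged related, and prone to differential attribution in a direction that the Discussion itself concedes. Comparison of harms of any cause rests on falls, injurious falls and participant-reported service use at months 3, 6 and 12.

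The size is not known from the documents. The spurious differences of 1.6 to 12 points, and the half-widths of 6 to 9 points for an all-cause comparison, depend wholly on the assumed risks and related shares. They show the mechanism and its possible scale, not an expected result. The textual mismatch needs no assumption. If the full protocol already documents all serious events, the defect is that the Complications section misdescribes it, and the two must be reconciled.

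**What to change.** - *Complications section:* at the existing monthly contacts in all three arms, document every serious untoward occurrence, including deaths and inpatient admissions, with its date. Record relatedness as a separate field, not as a condition for documenting. The filter may stay for non-serious events.
- *Statistical analysis section:* report all-cause serious events by arm, with differences between arms and 95% confidence intervals. Call the non-serious analysis rates of possibly related complications.
- *Discussion:* limit the claim about FIMA to saying that it needs no relatedness judgement.
- *Full protocol:* if it already captures all serious events, align the article's description with it.

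The cost is one case report form used in every arm, wording changes in three sections, and slightly more documentation at the sites. No new contact or assessor is needed, because the open question is already asked every month.
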